**Fig. 1 Fig1:**
[figure not shown]
Schedule of enrolment, interventions, and assessments

**Fig. 2 Fig2:**
[figure not shown]
SPIRIT diagram

### Sample size

On the assumption of non-inferiority between hygiene measures and topical fusidic acid and between topical hydrogen peroxide and fusidic acid, and a predicted efficacy of fusidic acid of 80%, we require 160 patients in each intervention group. This provides 80% power and a one-sided *α* of 0·05 to show non-inferiority (10% margin) between each group and topical fusidic acid. In order to allow for 10% loss to follow-up and subsequent exclusions, recruitment of 178 participants to each group is required. Subsequent exclusions and loss to follow-up are defined as participants not available for follow-up at day 7 or when two digital images are not available to assess. Estimates of efficacy are extrapolated from published data [6, 19, 20], and the 10% margin was considered a clinically significant difference [21].

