### Trial design

TIARA is an open label, single-blind, non-inferiority randomised controlled trial with three parallel treatment groups. The primary endpoint is clinical improvement at seven days. Randomisation is performed 1:1:1 within each school clinic.

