### Statistical analyses

For baseline data, d**i**chotomous variables will be summarised as proportions of patients in each treatment group, differences between groups will be assessed using a chi-square statistic, and where small cell sizes (less than 5) are present, a Fisher’s exact test will be used. Continuous variables with an underlying normal distribution will be summarised as mean and standard deviation, and differences between groups will be assessed using Student’s *t*-test. Other distributions will be either transformed if suitable and *t*-tests performed with reporting of geometric means or distributions will be reported as median and interquartile range and differences in groups assessed using Wilcoxon rank non-parametric tests with Hodges-Lehmann estimates and 95% confidence intervals.

Analysis will be performed after completion of recruitment. Both hydrogen peroxide and simple hygiene groups will be compared independently with fusidic acid with 95% confidence interval. Non-inferiority will be defined as a treatment success rate of no more than 10% below that of the fusidic acid success rate. An intention to treat and per protocol analysis will be performed using all patients with available primary outcome data. Patients without primary outcome data or for whom caregivers withdrew consent to participate will not be included in the analysis.

To investigate predictors of treatment success, backwards stepwise random-effects logistic regression will be performed on a priori and other variables identified as different in baseline characteristics between randomisation groups.

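### With 160 evaluable children per group the trial has about 72% power on its stated inputs, not 80%; 80% power needs 198 per group

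*Protocol article*

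**What the plan says.** The Sample size section of the protocol article sets out the calculation. It starts from "On the assumption of non-inferiority between hygiene measures and topical fusidic acid and between topical hydrogen peroxide and fusidic acid", then gives the success rate and the result: "a predicted efficacy of fusidic acid of 80%, we require 160 patients in each intervention group". It continues "This provides 80% power and a one-sided" alpha of 0.05 "to show non-inferiority (10% margin) between each group and topical fusidic acid". It then allows 10% for loss to follow-up and later exclusions, which brings recruitment to 178 per group.

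Two other sections complete the inputs. The Statistical analyses section puts the margin on the scale of the difference in success rates: "Non-inferiority will be defined as a treatment success rate of no more than 10% below that of the fusidic acid success rate". The Trial design section fixes equal allocation: "Randomisation is performed 1:1:1 within each school clinic".

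No numerical success rate is given for hydrogen peroxide or for simple wound care.

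**The concern.** The section gives everything needed to recompute the sample size except a separate rate for the alternative treatments, and the answer is not 160. The stated power is therefore too high for both primary comparisons.

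This matters most if the result is inconclusive. A reader told that the trial had 80% power will treat a failure to show non-inferiority as stronger evidence against hydrogen peroxide or wound care than the design supports. The risk of such a false negative, for a treatment truly equal to fusidic acid, is more than a quarter in each comparison. The Introduction notes that hydrogen peroxide has already replaced fusidic acid in national guidance for mild-to-moderate disease, so the reading of an inconclusive result has practical weight.

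**Working it through.** **Inputs**

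- Success with fusidic acid: 80% (Sample size).
- Success with each alternative: not given as a number; taken as 80%, a true difference of zero.
- Margin: 10 percentage points (Sample size; scale from Statistical analyses).
- One-sided alpha 0.05, so z = 1.645; power 80%, so z = 0.842 (Sample size).
- Equal allocation (Trial design).

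**Required number per group**

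n = (z for alpha + z for power)² × [p₁(1−p₁) + p₂(1−p₂)] / margin²

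- (1.645 + 0.842)² = 6.183 (unrounded z values)
- 0.8 × 0.2 + 0.8 × 0.2 = 0.32
- n = 6.183 × 0.32 / 0.01 = 197.8, so **198 per group**

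The plan's 160 is not reproduced. The requirement is 38 per group higher, or 38/160 = 24%.

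**Power at the stated number**

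Power = Φ(margin / √(0.32/n) − 1.645)

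| Evaluable per group | Normal approximation | Exact binomial enumeration (Wald rule) |
|---|---|---|
| 160 | Φ(2.236 − 1.645) = 72.3% | 72.4% |
| 178 (no loss at all) | 76.2% | 76.5% |
| 198 | 80.0% | 80.0% |

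The Farrington–Manning method gives 71.8% at 160.

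**Allowance for loss**

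160 / 0.9 = 177.8, so 178: the plan's step is right. From the recomputed figure, 198 / 0.9 = 220 per group.

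**Does another method give 160 from the same inputs?**

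| Method or change | n per group |
|---|---|
| Farrington–Manning restricted variance | 201 |
| Continuity correction | 218 |
| One-sided alpha 0.025 | 252 |
| One-sided alpha 0.10 | 145 |
| 10% read as relative (8 points) | 310 |
| Risk-ratio scale | 174 |
| Odds-ratio scale | 267 |
| Equivalence (two one-sided tests) | 275 |

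None does.

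**What does give a figure near 160?**

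- 85% success in both groups: 6.183 × 0.255 / 0.01 = 157.7, so 158. Power at 160 is then 80.5%.
- Fusidic acid 80%, alternative truly better at 81%: 6.183 × (0.16 + 0.1539) / 0.11² = 160.4, so 161.
- Variance taken at 80% and 90%: 155.
- A one-sided superiority formula for 80% against 90%: 157.

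Each needs an input that the section does not state, or a design that this trial does not have.

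**The case against.** The strongest objection is that the section states only one success rate, "a predicted efficacy of fusidic acid of 80"%. Assuming non-inferiority is not literally assuming equality, and the section says its efficacy estimates come from published data not reproduced in the article. With the alternative at 81%, every number written in the section can stand and n comes to 161. This much is right: equal rates of 80% are an inference, and 85% is not the only route to a figure near 160. It does not rescue the text. Equality is the ordinary planning assumption when one rate is given, and if an advantage for the alternatives was built in, the calculation depends on an unstated input. It would also be a fragile one: with the alternative at 79%, 249 per group are needed. The Introduction itself reports that the earlier trial tended towards somewhat lower efficacy for hydrogen peroxide.

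A second objection is that 72% may not be the power of the analysis either. The Statistical analyses section plans 95% confidence intervals without saying whether they are one- or two-sided. If the lower limit of a two-sided interval decides, one-sided alpha is 0.025, power at 160 is Φ(2.236 − 1.960), about 61%, and 252 per group are needed. That is a fair caution. The 72% applies at the alpha stated in the Sample size section and must be quoted with it.

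Third, the error leaves the margin, the type I error and the decision rule untouched, and confidence intervals will show the imprecision whatever the plan says about power. That is true and limits the consequence to planning and interpretation, but the power statement is still wrong as written.

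**Conclusion.** The concern holds. On the stated inputs, with both groups at 80% success, 160 evaluable children per group give 72.3% power, 7.7 points below the 80% claimed, and the false-negative risk in each comparison is about 28% instead of 20%. The claimed power needs 198 evaluable per group. Several standard non-inferiority methods were tried and none returns 160.

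The conclusion rests on equal true success rates, an absolute 10-point margin and one-sided alpha 0.05. The last two are in the protocol; the first is implied, not written. If a different rate was assumed, the stated basis of the calculation is incomplete or wrong, and the section still needs correction.

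**What to change.** Correct the Sample size section in one of two ways:

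1. Keep 160 and restate the power, for example: *160 evaluable participants per group give about 72% power to show non-inferiority at a 10-percentage-point margin, with one-sided alpha 0.05 and true success of 80% in both groups.*
2. If another planning value was used, such as 85% success in both groups, state it and support it from the cited data.

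In either case, give the assumed success rate in the alternative groups as a number, and make sure the alpha quoted with the power is the one the confidence interval will apply. Use the corrected power when an inconclusive comparison is interpreted.

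The cost is a few words and a less favourable power figure; no added recruitment is needed for the correction. Keeping the 80% claim at 80% success would instead require 198 evaluable and 220 recruited per group.

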### Recruitment

School health teams within recruiting schools will follow existing SOPs. Community health workers attend every class 3–5 days each week during the school term and ask children to self-identify any skin infections. These children are then reviewed by the school nurse. If the lesions are confirmed as impetigo, then eligibility for participation is assessed.

### Allocation concealment mechanisms and implementation

Randomisation is implemented by block randomisation within each participating school, sequence allocation code was written in R [22]. Children are randomly allocated (1:1:1) to topical fusidic acid, topical hydrogen peroxide, or simple hygiene measures. Participating schools are randomised separately to limit bias caused by excess recruitment to any individual arm within a single school*.* Allocation is performed by school nurses using the pre-generated codes contained in sealed, opaque, sequentially numbered envelopes. Both the participant and school nurse are aware of treatment allocation due to the appearance of the study medications (e.g. hydrogen peroxide has a silvery sheen) or lack of study medication in the simple hygiene measure arm. However, investigators, photograph reviewers, and laboratory staff are blinded to allocation.

## Data collection methods

### Demographic characteristics

Baseline characteristics of participants are collected at the time of randomisation and reported per randomisation group. The following demographic characteristics will be reported: age, gender, ethnicity, weight, history of pre-existing skin disease, allergies, and location of most severe lesion. All data is collected directly onto an electronic database used by school health clinics; additional trial questions have been created and added to this database by the study investigators. An equivalent paper proforma was designed by SP and included in the study materials for use if required.

### Primary outcome methods

The primary outcome of this trial is treatment success based on comparison of digital photographs taken at days 0 and 7. If clinical assessment leads to early discontinuation of the trial medication, this is also considered unsuccessful treatment. To aid standardisation, the primary outcome uses digital photographs independently assessed by blinded reviewers. The single largest lesion is photographed prior to commencing treatment, using a digital camera at a distance of 15 cm with an adhesive paper tape measure and unique study ID placed next to the lesion. Three digital images are taken at each data collection visit, and all are submitted to the study investigators. The single best quality image is then selected by the lead investigator (SP) for outcome assessment. Pairs of images are presented to three individual assessors blinded to intervention arm. The method of image presentation is randomised such that assessors are unaware of which image was taken first and which second. The outcome will be treatment success if the images are considered healed or improved and treatment failure if they are the same or worse, or if the reviewers cannot determine the outcome based on the digital images (e.g. due to poor quality images). Where there is discordance between assessor opinions, the majority opinion of two out of three reviewers will be considered the correct assessment. Patients removed from the trial protocol by school nurses or general practitioners before 7 days due to clinical deterioration will also be considered treatment failures. This process has been standardised previously in another large RCT of treatment of impetigo in remote access locations; different from our multicentre urban setting [21].

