### Intervention

All lesions are cleaned with saline and scabs gently removed. For the group randomised to fusidic acid, 2% fusidic acid ointment (DP Fusidic Acid, Douglas Pharmaceuticals Ltd, Auckland, NZ) is applied topically, and for the hydrogen peroxide arm, 1% hydrogen peroxide cream (Crystaderm, AFT Pharmaceuticals, Auckland, NZ) is applied topically. In both cases, an adequate amount to cover each lesion is used and dressing(s) then applied. A tube of appropriate topical medication is supplied for the child and/or caregivers to continue applications twice daily for 5 days with dressing changes. Participants allocated to simple hygiene measures receive no medication but a dressing is applied following the cleaning of the lesion(s). All participants are provided with supplies to allow them to clean and redress the wound twice daily for 5 days. Low adherent wound pads are used so as not to interfere with the wound healing process. In all groups, scabies is treated if present.

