### Modifications

All adverse effects, including pain, itch, or allergy to study medication, will be reported; the study medication must be withdrawn and the patient changed to routine treatment as per the SOP of the health clinic. If clinical deterioration while on study medication is identified by the school nurse, the study medication may be withdrawn at the nurse’s discretion. In this case, the patient will be changed to routine treatment as per the standard operating procedures of the health clinic.

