## Outcomes

### Primary outcome

The primary outcome of this trial is treatment success assessed by comparison of digital photographs or clinical deterioration based either on digital images or on nursing assessment leading to discontinuing trial medication.

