### Harms

Any adverse event will be reported; these are defined as any untoward medical occurrence in a subject without regard to the possibility of a causal relationship after entry into the study and until the completion of the study. At day 2 and day 7 of the trial, a safety check is performed by the school nurse to assess for rapid worsening of the impetigo or for adverse effects. If these occur, then the participant can be withdrawn from the trial at the discretion of the nurse. On day 2 and day 7, participants and/or caregivers are directly questioned regarding specific harms including itch, pain, redness, or any other adverse effects of medication. Any requirement for additional medical intervention is considered a potential harm. All harms will be reported.

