Because of the large and disparate pool of recruiters, it is important that the primary outcome is as comparable and unbiased as possible. Digital images allow for centralised assessment despite the distance between recruiting sites. However, this means the existing scoring system (SIRS) is not practical as variables included in the scoring such as warmth, pain, and itch are not amenable to visual assessment alone. For this reason, assessor defined scoring was used. Erythema is also one of the elements of the SIRS scoring system, and when assessing children with darker skin, this is often underestimated [23], leading to minimisation of the severity of lesions in those with darker skin. The use of digital images and multiple reviewers for the primary outcome aims to minimise the bias inherent in the majority of previous studies on impetigo and provide a reproducible outcome, consistent with real world improvement. This remains an imperfect measure as it is dependent on good quality digital images and reviewer defined assessment. Due to the visible difference in the topical medications, neither school nurses nor participants could be blinded to treatment. This introduces a potential element of bias for those removed from the study early due to clinical treatment failure. It was considered unfeasible to introduce a placebo medication to the simple wound hygiene group. Potentially, any ointment without antimicrobial properties could provide an environment for bacterial growth or negatively affect bacterial growth, potentially changing the outcome for this group.

Topical antibiotics remain the mainstay of treatment for mild-to-moderate impetigo in many countries around the world, including New Zealand. Widespread community use and a tendency for prolonged courses mean that they excel at inducing antimicrobial resistance. Evidence for antiseptic use or simple hygiene measures in impetigo is extremely limited: this will be only the second trial to compare these topical antiseptics and antibiotics and the first to take current antimicrobial resistance patterns into account. On the background of a worldwide increase in antimicrobial resistance and with increasing recognition of the importance of antimicrobial stewardship, it is timely to re-address the evidence for the role of antiseptics and antibiotics in the treatment of impetigo. This is only possible, however, if the most affected communities are appropriately engaged in this research.

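### The early-failure part of the primary endpoint is worded three ways, and two of the wordings turn on stopping a medication that the wound-care arm does not receive

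*Protocol article*

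**What the plan says.** The main route to the primary outcome is a day 0 versus day 7 photograph comparison by three blinded graders. A second route scores a child as a failure because of early stopping. The protocol article describes it three times:

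- Primary outcome methods, near the start: "If clinical assessment leads to early discontinuation of the trial medication, this is also considered unsuccessful treatment".
- Primary outcome methods, near the end: "Patients removed from the trial protocol by school nurses or general practitioners before 7 days due to clinical deterioration will also be considered treatment failures".
- Outcomes, Primary outcome: "clinical deterioration based either on digital images or on nursing assessment leading to discontinuing trial medication".

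Related text:

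- Modifications, on adverse effects including pain and itch: "the study medication must be withdrawn and the patient changed to routine treatment as per the SOP of the health clinic". On deterioration: "the study medication may be withdrawn at the nurse’s discretion".
- Harms, on rapid worsening or adverse effects: "then the participant can be withdrawn from the trial at the discretion of the nurse".
- Intervention: the simple hygiene (wound-care) arm is given cleaning and dressings, with no medication.
- Allocation concealment: nurses and participants know the allocation; investigators, photograph graders and laboratory staff do not.
- Sample size treats a child with no day 7 follow-up, or without two images, as an exclusion or loss. Statistical analyses leaves out children without primary outcome data.

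**The concern.** The primary endpoint of a non-inferiority trial should classify the same event in the same way in every arm. Here the classification depends on which sentence is followed, and two of the three sentences depend on an act, stopping a medication, that cannot occur in the wound-care arm.

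Any extra failures that this creates in one arm feed directly into the difference that is compared with the 10-point margin. They also enter through decisions by staff who know the allocation, outside the blinded photograph grading that protects the rest of the endpoint.

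**Working it through.** **Step 1. The three wordings compared**

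| | Reason needed | Who decides | Act that counts | Fits wound care? |
|---|---|---|---|---|
| A. Methods, first sentence | none stated | not named | stopping trial medication | not literally |
| B. Methods, later sentence | deterioration | nurse or general practitioner | removal from the protocol before day 7 | yes |
| C. Outcomes, nursing route | deterioration | nurse | stopping trial medication | not literally |

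**Step 2. Apply each wording to the same events**

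| Event before day 7 | A | B | C |
|---|---|---|---|
| Cream arm, stopped for itch or pain only | failure | not a failure | not a failure |
| Wound care, switched for itch or pain only | not covered | not a failure | not a failure |
| Cream arm, nurse stops cream and removes child for deterioration | failure | failure | failure |
| Wound care, nurse switches for deterioration | not covered | failure | not covered |
| Cream arm, general practitioner stops cream and removes child for deterioration | failure | failure | not named |

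If A, B and C are added together, deterioration is captured in all arms, but an adverse-effect stop is a failure only in the cream arms. If B and C govern, A adds nothing and an adverse-effect stop is not an automatic failure in any arm. The text does not say which reading applies.

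**Step 3. Exclusions.** A child removed early who has no day 7 image fits both the failure rule and the Sample size description of an exclusion. Neither Sample size nor Statistical analyses says that early failures are kept.

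**Step 4. Size, as an illustration only.** The documents give no early-stop rate, so the rates below are assumptions.

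*Shift in the estimate.* Assume that 80% of children stopped for itch or pain would have been graded a success (the protocol's predicted fusidic acid efficacy). Under wording A, shift in points = 100 × proportion stopped × 0.80. With 2%, 3% or 5% of the fusidic acid arm stopped, the wound-care comparison moves 1.6, 2.4 or 4.0 points toward non-inferiority. In the other direction, each 1% of wound-care children removed early who would have been graded improved moves it by up to 1 point.

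*Effect on error rates.* Inputs from Sample size: 160 per group, 80% success, margin 0.10, one-sided alpha 0.05. The probability of declaring non-inferiority is Φ[(0.10 − (pC − pT))/SE − 1.645], with SE = √{[pC(1 − pC) + pT(1 − pT)]/160}.

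With pC = pT = 0.80, SE = √(0.32/160) = 0.0447 and the power is Φ(2.236 − 1.645) = 72.3%. The stated 80% is not reproduced: this formula needs 198 per group. That is a separate matter, and 72.3% serves here only as the starting value.

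| Extra failures in one arm | Children of 160 | Power, if in an experimental arm (true difference 0) | False non-inferiority, if in the fusidic acid arm (true deficit 10 points) |
|---|---|---|---|
| 0 | 0 | 72.3% | 5.0% |
| 1 point | 1.6 | 63.7% | 7.5% |
| 2 points | 3.2 | 54.5% | 10.8% |
| 3 points | 4.8 | 45.2% | 15.0% |

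Statistical analyses specifies a 95% interval. If that is two-sided (one-sided 0.025), the same rows give power of 60.9%, 51.4%, 42.0% and 33.2%, and false non-inferiority of 2.5%, 4.0%, 6.1% and 8.9%.

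**The case against.** The best defence is that the general sentence should be read through the two specific ones. Wording A follows directly on the photograph assessment and can be taken as its clinical counterpart, that is, a lesion judged to be failing. Deterioration is then the single trigger, and a stop for itch alone is not an automatic failure. This is a fair reading, but the text does not require it, and the sentence as written sets no reason.

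Four stronger readings are tempting and are not supported:

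- *The early-failure rule cannot be applied to wound care at all.* It can: wording B is arm-neutral and names general practitioners as well as nurses.
- *Modifications and Harms flatly contradict each other.* Only in part. One concerns stopping the medication and the other leaving the trial, and a mandatory stop can coexist with discretionary withdrawal. The two sections still need reconciling, because neither says how such a child is scored.
- *The nurse bias was overlooked, or no blinded check exists.* The Discussion names it: "This introduces a potential element of bias for those removed from the study early due to clinical treatment failure". The article describes no mitigation, but it condenses a fuller protocol that may contain one. Adverse events are in any case to be compared across arms.
- *The trial is biased toward non-inferiority by a known amount.* The rates in Step 4 are assumed and the two mechanisms pull in opposite directions. In the hydrogen peroxide comparison both arms have the adverse-effect route, so its effects partly offset.

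It is also true that reactions to a product arise only in arms given one. That is inherent in a design without placebo, which the Discussion justifies. Whether intolerance counts as failure is an endpoint choice; the fault is that the choice is not stated.

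**Conclusion.** The point holds as an inconsistency in the primary endpoint definition that should be corrected. The three wordings differ on reason, decision-maker and act. Read literally, they allow an adverse-effect stop to be a failure in the cream arms only, and they leave a wound-care child switched for deterioration clearly captured by one sentence alone. Whether early failures without a day 7 image stay in the analysis is also not stated.

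These conclusions rest on the text and need no assumption about rates. The size and net direction of any bias cannot be determined from the documents. Step 4 shows only that a handful of children per arm would matter against a 10-point margin. The trial remains interpretable if the definition is settled before unblinding.

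**What to change.** 1. **One definition.** Replace the three wordings with a single arm-neutral one. For example: a switch from the allocated management to routine treatment before day 7 because of deterioration, made by a nurse or general practitioner, is a failure in every arm.
2. **Retention.** State that these failures stay in the analysis whether or not a day 7 image exists, so that the exclusions in Sample size and Statistical analyses do not remove them.
3. **Adverse-effect stops.** State one scoring rule, the same in all arms, and a sensitivity analysis that scores them the other way. Either choice is open to debate: a photograph taken after the switch credits the effect of routine treatment to the allocated arm.
4. **Blinded check.** Where a nurse makes the switch, take the standard photographs first and have the existing blinded graders compare them with day 0. The nurse-based failure stands in the primary analysis; a sensitivity analysis puts the blinded grade in its place.
5. **Clinical text.** The clinical team should reconcile Modifications and Harms on withdrawal for adverse effects. Which rule stands is for them to decide.

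The cost is protocol wording, two sensitivity analyses and one extra photograph set per nurse-made switch, using the cameras and graders already in place. The drawback is that these photographs are graded at a time other than day 7 and do not cover removals by general practitioners.
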